**Summary**

High cognitive load of nurses is a common problem in intensive care unit, which is associated with nurses' poor performance of activities, as well as related to poor patient outcomes. It remains unclear whether Artificial Intelligence Assisted Prevention and Management for **Delirium** (*AI-AntiDelirium*) results in reduction of cognitive load and enhances adherence to delirium intervention in ICU nurses. We aim to assess the effectiveness of *AI-AntiDelirium* on cognitive load and adherence to delirium interventions of ICU nurses and the impact of ICU delirium. This is a multicentre, prospective, cluster randomised controlled clinical trial comparing the impact of *AI-AntiDelirium* and PADIS guideline for ICU nurses. A total of six ICUs in two hospital will be randomised in a 1:1 ratio to receive either *AI-AntiDelirium* (intervention group) or PADIS guideline (control group), with target sample size of 78 ICU nurses. The primary endpoint will be the adherence to delirium interventions. The secondary endpoints will be the cognitive load which measured by an instrument for measuring different types of cognitive load (MDT-CL). The endpoints of patients included incidence and duration of ICU delirium, length of ICU and in-hospital stay, ICU and in-hospital mortality. Outcome assessments will be conducted by investigators who blind to group assignment. The repeated measures analysis of variance (RMANOVA) will be performed to detect the difference in adherence and cognitive load between groups. Generalized estimation equation will be performed to

test the difference in patient outcomes.

## **Background**

Cognitive load refers to the total amount of cognitive resources that a person needs to process cognitive activities, and is composed of three different types: intrinsic CL, extraneous CL and germane CL. Higher CL, which exceeds one's working memory resource capacity, has been identified as one of the most important problems in providing intensive care. It negatively impacts nurses and their patients, which can lead to irritability, memory impairments and mental fatigue of nurses, is detrimental to performance of activities, reduced learning capacity for acquiring knowledge, and also results in poor patient outcomes and compromises patient safety. The more complicated are the activities performed by nurses, the higher the CL are required, which will hinder the adherence to implement nursing activities.

Nursing care in intensive care units (ICU) is characterized by extremely demanding caseloads, performance of complicated activities and making complex decisions. One example is the complex care required in ICU delirium prevention and management interventions. ICU delirium is a common complication of ICU patients with an high incidence of 70% to 87%, and associated with longer hospital length of stay (LOS) and increased mortality. Therefore, the Clinical Practice Guidelines for the Prevention and Management of Pain, Agitation/Sedation, Delirium, Immobility, and Sleep Disruption in Adult Patients in the ICU (PADIS guideline) recommend use of the ABCDEF bundle as a way to prevent and manage ICU delirium, which focuses on eliminating ICU delirium risk factors. However, adherence to the ABCDEF bundle is sub-optimal in routine clinical care. Previous studies have demonstrated that various barriers may hinder the adherence to

implement the bundle, such as heavy workload on nursing care records, complexity algorithm of assessment tools, struggle to collect and remember numerous risk factors through multiple channels, lack of knowledge about ICU delirium^27. Working on complicated activities results in lowered speed for receiving and processing information, decreased capacity of working memory and requires higher cognitive load (CL).

Considering the negative consequence of high CL from delirium care, it is important to provide ICU nurses with the aid of a tool that can reduce CL of nursing care in ICU delirium. With the rapid development of information technology, clinical decision support system (CDSS) has been widely used in most hospitals in worldwide for disease assessment, management and record. The CDSS play an important role in clinical nursing care, and also commonly used in cognitive psychology. It can collect, sort, classify and establish logical relationship of the patient information, and also make use of alert, information feedback to provide decision support during disease diagnosis, treatment and nursing activities. Several studies have shown that CDSS can help medical staff to recall less clinical information, which lead to a significant reduction in CL and improvement the adherence to implement nursing interventions.

Therefore, we developed an Artificial Intelligence Assisted Prevention and Management for Delirium (*AI-AntiDelirium*) which including ABCDEF bundle intervention, risk factors and assessment tools of ICU delirium. The aims of this study are to assess the effectiveness of *AI-AntiDelirium* on adherence and cognitive load of ICU nurses, as well as clinical outcomes related to ICU delirium.

## Methods

The protocol is developed according to the Standard Protocol Items:

Recommendations for Interventional Trials (SPIRIT).

### **Study design and setting**

The *AI-AntiDelirium* to improve adherence to delirium intervention of ICU nurses is a multicenter, cluster randomized controlled trial (RCT), six ICUs with higher incidence of ICU delirium in two tertiary hospitals are selected, which represent three types of ICUs (2 Surgical ICU [SICU], 2 Respiratory ICU [RICU] and 2 Cardiac ICU [CICU]) as well as the variety of the samples, and the promise of ICU staff to improve the quality of care in ICU delirium. A tertiary hospital is a 1000-bed university-affiliated teaching hospital, with 42 adult ICU beds in the 3 participating ICUs. B tertiary hospital has 730 beds and 3 eligible ICUs of 46 beds, which the annual admission rate is about 850 patients. They have fully implemented hospital informatization. The study will be conducted during the period 2022 - 2023. Figure 1 shows the design of the study.

[figure not shown]

**Figure 1 study design**

*AI-AntiDelirium*, Artificial Intelligence Assisted Prevention and Management for Delirium;

**PADIS guideline**, Clinical Practice Guidelines for the Prevention and Management of Pain, Agitation/Sedation, Delirium, Immobility, and Sleep Disruption in Adult Patients in the ICU;

## Participants

Registered Nurses (RN) who worked in included ICUs were all recruited. Nurses were eligible for the study if they (1) had a minimum of 1 year experience in intensive care; (2) worked full-time in the unit; and (3) consented to participate in this study. Nurses who were on study programs outside the hospitals or on leave for various reasons during the study period were excluded.

## Intervention Groups

Prior to the study, an educational program is delivered by researchers, including knowledge regarding ICU delirium risk factors, assessment tools (Confusion Assessment Method for the Intensive Care Unit [CAM-ICU], Intensive Care Delirium Screening Checklist [ICDSC]), and ABCDEF bundle interventions. Except that, eligible ICU nurses are trained with how to operate the *AI-AntiDelirium*. We developed the *AI-AntiDelirium*, which included the four main modules: ICU delirium assessment module (Figure 1A), risk factors assessment module (Figure 1B), nursing care plan module (Figure 1C) and nursing checklist module (Figure 1D).

[figure not shown]

**Figure 1. Modules of Application**

A: ICU delirium assessment tools and results; B: risk factors assessment and predictive risk value;  
C: nursing care plan; D: nursing checklist

ICU nurses in the intervention group will provide ICU delirium nursing care based on *AI-AntiDelirium*. Each day, the nurse will assess ICU patients with the assistance of *AI-AntiDelirium*, which can recognize ICU delirium, automatically

present risk factors and tailor evidence-based prevention or management strategies of ICU delirium. During the study, the nurse who receive ICU delirium training clicks the icon of *AI-AntiDelirium* on the Personal Digital Assistant (PDA) to enter the system.

- a. **Register:** click the icon of register → enter the user name → enter the password → choose the hospital and department → submit;
- b. **Log in:** enter the user name and password → log in.
- c. **Add the patient:** click the button “+” → enter the medical record No. → enter patient name → enter patient gender → enter patient age → enter patient bed number → enter patient admission time.
- d. **Diagnose ICU delirium:** click the button of delirium assessment → select a delirium assessment tool (CAM-ICU or ICDSC) → complete the item one by one according to the prompts → the *AI-AntiDelirium* will automatically display whether the patient has delirium or not.
- e. **Identify patients ICU delirium risk factors:** click the button of “risk factors assessment” → complete a brief risk factor assessment evaluation list, including three categories, predisposing (e.g. hearing impairment, vision impairment), disease-related (e.g. infection, pain), iatrogenic and environmental factors (e.g. mechanical ventilation, sedative use) → the *AI-AntiDelirium* will automatically report personalized risk factors of the patient → the *AI-AntiDelirium* will automatically show the risk prediction value in developing delirium according to a dynamic ICU delirium prediction rule.
- f. **Confirm nursing care plan:** click the button of “nursing care plan” → the *AI-AntiDelirium* will automatically present individual ICU delirium prevention or management care plan according to the result of risk factors assessment → the ICU

nurse checks and confirms that all interventions for the patient are appropriate and feasible.

g. **Implement individual, risk factors targeting interventions:** click the button of “nursing checklist” → the *AI-AntiDelirium* will automatically automatically display the specific execution time of each intervention basing on the results of nursing care plan → the nurse implements individual interventions during the whole shift and records reasons why the patient do not receive these interventions → the nurse clicks on the measure after implements it → the *AI-AntiDelirium* automatically record the nurse's name and the time of execution.

### **Control group**

Prior to the study, an educational program related to ICU delirium is delivered by researchers, the content are same to intervention group. In addition, nurses are trained with the usage of PADIS guideline. During the study, nurses will provide ICU delirium nursing care according to PADIS guideline, including ICU delirium risk factors, assessment tools (CAM-ICU, ICDSC), and ABCDEF bundle intervention.

a. **Diagnose ICU delirium:** The nurse chooses one instrument (CAM-ICU or ICDSC) to assess ICU delirium occurrence and completes the item one by one. The nurse manually records the assignment score of each item, and calculates the final total score, and then they judge whether the patient develops delirium or not according to the rule of assessment tool.

b. **Identify patients ICU delirium risk factors:** The ICU nurse fills out a brief risk factor assessment for delirium (the content same to intervention group). The nurse makes decision by themselves about patient's current risk factors according to the risk factors assessment results and manually calculates the patient's current risk of developing ICU delirium according to the dynamic ICU delirium prediction rule.

c. **Implement individual, risk factors targeting interventions:** The nurse extracts nursing intervention from the PADIS guideline according to the result of patient' specific risk factors, and records the intervention in nursing care records, and implements appropriate subset of interventions.

### **Outcomes**

Endpoint assessment will implement by trained research staffs who will not involve in the clinical nursing care of patients.

**The primary outcome is adherence to the intervention, which** is defined as the adherence of nurses to implement ICU delirium and risk factors assessment, delirium prevention and management interventions every day. The reasons for non-adherence will record daily by the intervention staff.

- a. Adherence to ICU delirium assessment was calculated by dividing the number of actions to number of theoretical assessment. The theoretical ICU delirium assessment for each nurse per day was defined as twice daily multiply the number of patients cared by the nurse.
- b. Adherence to ICU delirium risk factors assessment was calculated by dividing the number of actions to number of theoretical risk factors assessment. The theoretical risk factors assessment for each nurse per day was defined as once daily multiply the number of patients cared by the nurse.
- c. Adherence to ICU delirium prevention or management intervention was calculated by dividing the number of actions to number of theoretical interventions implementation

**Secondary endpoints** will include cognitive load of nurses, **which** defined as the total amount of limited cognitive resources that a person is occupied during a cognitive task. Cognitive load was assessed by means of an instrument for measuring

different types of cognitive load (MDT-CL) with **ten-item**, which had been successfully used to distinguish different types of cognitive load. Each item score from 0 to 10, the higher of the score, the higher of the cognitive load. Cronbach's  $\alpha$  of Chinese version MDT-CL was 0.818, cronbach's  $\alpha$  values in measurement of intrinsic CL (Items 1, 2, and 3) was 0.879; cronbach's  $\alpha$  values in measurement of extraneous CL (Items 4, 5, and 6) was 0.878; cronbach's  $\alpha$  values in measurement of germane CL (Items 7, 8, 9, and 10) was 0.946.

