### **Sample size**

The aim of the cluster RCT is to improve the adherence to delirium intervention of ICU nurses by using the *AI-AntiDelirium* compared to the PADIS guideline. We expect that adherence to delirium intervention in the *AI-Antidelirium* group is 80% and PADIS guideline group is 50%, suggesting that *AI-Antidelirium* has clinical significance in improving the adherence to delirium intervention of ICU nurses. Sample size calculations showed that 12 nurses in each cluster will provide 80% power and a two-sided significance level ( $\alpha$ ) of 0.05, with an intracluster (within-unit) correlation of 0.002. In addition, taking into account possible dropout rate of 10%, we plan to enroll 13 nurses in each ICU, the final sample size is 78 (13\*6) nurses.

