### **Statistical methods**

All data will be analysed using SPSS version 21.0 (SPSS Inc Chicago, Illinois) with an intention-to-treat (ITT) principle, missing data will be imputed using multiple imputations. Statistical analyses will be done by a statistician who is blind to intervention allocations. Continuous variables will be described as means and standard deviation (SD) for normally and medians and interquartile range for abnormally distributed data. Comparisons between groups will performed with the Mann-Whitney U-test (analysis of variance) or Wilcoxon test, including cognitive load, adherence, duration of ICU delirium, length of ICU stay, length of stay in the hospital. Categorical variables will be expressed as frequencies and percentages. Chi-Square test or Fisher's exact test will used to examine between-group differences among incidence of delirium, baseline delirium risk factors and demographics.

Considering the correlation that results from repeated measurements on the same individual, repeated measures analysis of variance (RMANOVA) is used to analyze the multiple measurements variable which is gathered on everyday, such as CL,

adherence of ICU nurses. We will adjust for age, educational level, years of ICU experience, level of knowledge, since these factors were likely to be associated with adherence and CL. Bonferroni post hoc tests were used to assess within-group changes over time, as well as between-group differences during study intervention. Differences in incidence of delirium between groups are analyzed after adjusting for demographic variables using generalized estimation equation. All tests are two-tailed, and P - value < 0.05 is considered statistically significant.

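### The single primary outcome, adherence, is defined only as three separate ratios, with no combining rule, lead ratio or success rule, while every test is called significant at P < 0.05

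*Protocol*

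**What the plan says.** The Outcomes section states the primary outcome in the singular and describes it as "the adherence of nurses to implement ICU delirium and risk factors assessment, delirium prevention and management interventions every day". Three definitions follow:

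- (a) "Adherence to ICU delirium assessment was calculated by dividing the number of actions to number of theoretical assessment". The denominator is two assessments a day times the number of patients the nurse cares for.
- (b) "Adherence to ICU delirium risk factors assessment was calculated by dividing the number of actions to number of theoretical risk factors assessment". The denominator is one assessment a day times the number of patients.
- (c) "Adherence to ICU delirium prevention or management intervention was calculated by dividing the number of actions to number of theoretical interventions implementation". The text does not say how the theoretical number of interventions is counted.

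Table 1 gives each of the three its own outcome row. Sample size works from one pair of rates, 80% against 50%, introduced with "We expect that adherence to delirium intervention in the", and does not tie that pair to (a), (b), (c) or a combination.

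Statistical methods first says "Comparisons between groups will performed with the Mann-Whitney U-test (analysis of variance) or Wilcoxon test, including cognitive load, adherence". It then says that "repeated measures analysis of variance (RMANOVA) is used to analyze the multiple measurements variable which is gathered on everyday", again with adherence as an example. The Summary names repeated-measures ANOVA alone for adherence. The significance rule is general: "All tests are two-tailed, and P - value < 0.05 is considered statistically significant". The one multiplicity step, Bonferroni, applies to post hoc comparisons over time and between groups; nothing extends it to the three ratios.

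**The concern.** A primary outcome should yield one confirmatory answer, or several answers with a stated rule for reading them together. Here the label is singular, the definitions are three, and the sample size rests on one contrast. If the ratios disagree, the protocol does not let a reader decide whether the trial met its primary objective. An analyst following the text could report any ratio with P < 0.05 as a positive primary result, and could choose between two between-group tests for it. The stakes are the error rate behind the main claim, and whether the planned power belongs to the quantity on which that claim is made.

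**Working it through.** **Step 1. Reproduce the planned size.** Inputs from Sample size: 80% versus 50%, two-sided alpha 0.05, power 80%, 12 nurses per ICU, intracluster correlation 0.002. Randomisation gives 6 ICUs at 1:1, so 3 per arm.

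- Unpooled two-proportion formula: (0.50×0.50 + 0.80×0.20)×(1.960 + 0.842)² / 0.30² = 0.41×(2.802)² / 0.09 = 35.76 per arm.
- Design effect: 1 + (12 − 1)×0.002 = 1.022.
- 35.76×1.022 = 36.54 per arm, or 12.18 per ICU, against the stated 12.
- Power at 36 per arm: the effective size is 36/1.022 = 35.23, the standard error √(0.41/35.23) = 0.1079, and 0.30/0.1079 = 2.781. Power = Φ(2.781 − 1.960) = 79.4%.

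The plan's figure therefore reproduces, for **one** test of **one** adherence measure at the full 0.05.

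**Step 2. Three tests at 0.05, success on any one.** The any-one rule is an assumption; the protocol states no rule. The correlation between the ratios' test statistics is also not given, so a range is shown.

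- Independent: 1 − 0.95³ = 14.3%.
- Correlated: the chance that at least one of three equally correlated standard normal statistics exceeds 1.960 in absolute value, by numerical integration.

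| Correlation | At least one of three significant | All three significant |
|---|---|---|
| 0 | 14.3% | 0.01% |
| 0.5 | 12.5% | 0.3% |
| 0.7 | 10.9% | 0.9% |
| 0.8 | 9.8% | 1.4% |
| 0.9 | 8.4% | 2.3% |

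The last column is the rate if success required all three. It stays below 5% and approaches 5% only as the correlation approaches 1.

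**Step 3. Two tests per ratio.** If either the rank test or the repeated-measures test could carry a ratio, the any-one rate rises further. With an assumed correlation of 0.7 to 0.95 between the two tests, simulation gives about 18–23% when the ratios are uncorrelated, 16–20% at correlation 0.5 and 12–16% at 0.8.

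**Step 4. Price of an alpha split.** Bonferroni uses 0.05/3 = 0.0167 per ratio, two-sided critical value 2.394. Power at 36 per arm becomes Φ(2.781 − 2.394) = 65%, down from 79%. Restoring 80% would need 0.41×(2.394 + 0.842)² / 0.09×1.022 = 48.7 per arm. A fixed sequence tests the first ratio at the full 0.05, so that ratio keeps the planned 79%.

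All these rates take each test to be valid at its nominal 5%. Whether the adherence tests allow for clustering by ICU is a separate matter.

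**The case against.** The strongest reply is that the protocol declares one primary outcome and nowhere says that success on one ratio is enough, so no inflated error rate follows from the text. The ratios come from the same nurses on the same days and share patient load, so high correlation is plausible and the inflation would then be smaller. That stands. A reader might infer that the trial's false-positive rate **is** 10–14%; the documents do not support this, because the figure needs an any-one rule and a correlation between 0 and about 0.8, neither of which is stated.

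The two-test point is also weaker than the three-ratio point. The Summary names only repeated-measures ANOVA for adherence, and Statistical methods justifies it by the daily repeated measurements and attaches the covariate adjustment to it. The rank tests sit in a general paragraph beside the descriptive statistics. Adherence is nevertheless listed there by name, so the text remains inconsistent.

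Two further inferences do not hold. One is that 80% versus 50% describes ratio (c): the Summary uses almost the same phrase for the whole primary endpoint, so the link is not established. The other is that (c) must lead because software prompts could lift (a) and (b) without more preventive care. Under Intervention Groups, (c) also runs on a software checklist with displayed execution times, so prompting does not separate it from the other two. Moreover, (c) has the least defined denominator: the care plan is generated by the software in one arm and extracted from the guideline by the nurse in the other.

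Finally, alpha allocation and test hierarchy are often left to the SAP, which is not at hand. That would excuse missing detail. It does not excuse a protocol whose outcome definition, sample size and significance rule do not fit together.

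**Conclusion.** The point holds as an ambiguity in the primary outcome that leaves the error rate of the primary claim uncontrolled. With any-one success and one test per ratio, the rate could reach about 14%, falling to 8.4% at correlation 0.9; using both tests would raise it. With an all-three rule it would be below 5%. The protocol does not let the reader choose between these readings, and that is the defect. The sample size supports one contrast at 0.05 and does not say which. The change should be made before analysis, but the documents do not show that the trial's error rate has any particular value, nor that (c) is the only sound primary.

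**What to change.** Before any unblinded analysis, amend the protocol as follows:

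1. Designate one ratio, or one explicitly defined composite, as the primary outcome. Alternatively, test the three in a prespecified fixed sequence, each at 0.05 and only while all earlier ones are significant. This needs no alpha split, so the first ratio keeps the planned power of about 79% instead of about 65% under Bonferroni.
2. State which measure the 80% versus 50% assumption refers to. If it is not the designated primary, give the assumption for the one that is.
3. If (c) leads, define its denominator identically in both arms.
4. Keep the repeated-measures model named in the Summary as the only between-group test of adherence, and remove adherence from the Mann-Whitney/Wilcoxon list.

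Cost: no additional nurses, but more than an editorial change. Participant timeline puts the start of data collection in November 2022, so this is an amendment to the primary outcome of a running trial and should be dated and justified. A significant result on a non-lead ratio alone would no longer count as primary success.
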